## Abstract

Population aging will be on the public health agenda in the coming decades. By 2050, 16% of the world’s population will be aged 65 and above, mostly living in middle- and low-income countries. In Brazil, the aged population will triple by 2050, from less than 20 million to approximately 65 million, making it the sixth largest aged population in the world. Population aging is associated with an increase in the prevalence of chronic non-communicable diseases, which in turn promotes a functional decline in people who age. This often leads to limitations in daily life and dependence, with clear implications for the quality of life and health costs. In 2015, the World Health Organization proposed the concept of intrinsic capacity (IC) as a multidimensional health indicator that encompasses the essential physical and mental capabilities for people to perform what they need and like in daily life, regardless of the chronological age. In practice, IC was operationalized in five health domains, namely, cognitive, psychological, sensory, locomotor, and vitality. These domains, which are evaluated together and over time, offer the function parameters necessary to understand different, person-centered aging trajectories. Prevention of age-associated functional decline has not been studied well. Literature lacks studies that indicate the expected values for different IC trajectories related to aging, with or without disability. Few studies have analyzed IC as a risk factor for compromising the functional ability (FA) of the elderly, which is measured by the degree of dependence in activities of daily living, the risk of falls, and early mortality, while controlling for all known risk factors for functional decline. The cohort study proposed here, called “Longevity with Functionality (LONGFUN),” addresses the growing importance of evaluating the indicators of IC in a prospective way, creating a single indicator, and relating it to the FA of the aged population.

## Introduction

Population aging will be on the public health agenda in the coming decades. By 2050, 16% of the world’s population will be aged 65 and above, mostly living in middle- and low-income countries. In Latin America and the Caribbean, estimates indicate that this age group will represent 19% of the entire population (World Health Organization, 2015). In Brazil, the population aged 60 and over will triple by 2050, increasing from less than 20 million to approximately 65 million (15 million aged 80 or over), making it the sixth largest elderly population in the world (Ramos et al., 1987; Fapesp, 2016).

While population aging represents an improvement in the population’s social and health indicators, there are countless challenges accompanying this demographic transition. For example, longevity lived with good functionality, one of the pillars of quality of life (QoL) among the elderly, will be a privilege for some, but many will experience limitations in their daily lives in the final third stage of life (Rosa et al., 2003).

Population aging is associated with an increase in the prevalence of chronic non-communicable diseases (NCDs), which in turn promotes functional decline in people who age; this often leads to limitations and dependence in daily life, with clear implications for the QoL and healthcare costs (Calderón-Larrañaga et al., 2019; Costa Filho et al., 2018; Miranda et al., 2016; Ramos, 2003). The cohort study proposed here, called “Longevity with Functionality (LONGFUN),” addresses the growing importance of evaluating the rate of progression of functional limitations with age and factors associated with the loss of the ability of individuals to live with independence and autonomy.

### Prevention of functional losses

Prevention of age-associated functional decline is still not well-studied. Some existing studies show that it is possible to increase the physical activity in sedentary elderly people (Novais et al., 2019) and the cognitive ability of elderly people with mild cognitive impairment through digital inclusion workshops (Irazoki et al., 2020; Vicentin et al., 2018). We can also improve the mental state of older adults with mindfulness in late-life depression (Mapurunga et al., 2020; Mathur et al., 2016) and aid in hearing and vision with increasingly accessible prostheses (Lin et al., 2013; Whitson and Lin, 2014). In addition, physical independence can be improved with assistive technology, which range from the simplest (cane) to the most sophisticated (robots) (Haufe et al., 2019; Lichtenberg, 2024).

### Intrinsic capacity

In 2017, the World Health Organization (World Health Organization, 2017) proposed the concept of intrinsic capacity (IC). This is a multidimensional health indicator that encompasses the essential physical and mental capabilities for people to perform what they like, regardless of their chronological age. This approach modifies the negative stereotypes linked to old age by emphasizing the positive attributes of health and the physiological reserve that individuals can develop and maintain throughout life.

In practice, IC has been operationalized in five domains: vitality, mobility, sensory, cognitive, and psychological. These domains, which are evaluated together and over time, offer the functional parameters necessary to understand different, people-centered aging trajectories during the Decade of Healthy Aging (2020–2030) (Dixon, 2021; Rudnicka et al., 2020).

## Rationale

Research shows that the prevalence of age-related functional disability in Brazil is large and still growing (Giacomin et al., 2018; Lima-Costa et al., 2022), but we do not know if this phenomenon is occurring in terms of IC. Recent research shows that IC is a valid measure for healthy aging in a country such as Brazil (Aliberti et al., 2022). A Latin American study showed that the reduction of IC in old age, including one or more of the factors in IC’s five domains, has a negative impact on the functional ability (FA) in the elderly (Prince et al., 2021). These associations must be reassessed with longitudinal studies in new environmental contexts such as the elderly population in Brazil (Martin and Ortuño, 2019).

Literature lacks studies with IC as the outcome variable, which is needed to indicate the normality values for different IC trajectories related to aging, with or without disability. Few studies have analyzed IC as a risk factor for compromising the FA of the elderly, measured by the degree of dependence in the performance of day-to-day activities, the risk of falls, and early mortality, while controlling for all possible known risks for functional losses—clinical, biological, genetic, and social (Prince et al., 2021). There are studies that point out that IC can predict the decline in activities of daily living (ADL) and instrumental activities of daily living (IADL) even after adjusting for sociodemographic factors and chronic diseases (Lu et al., 2021; Prince et al., 2021; Fong, 2019; Jonkman et al., 2018; Pan et al., 2021).

The key medical literature gaps that this proposed research aims to fill is how a set of comprehensive factors such as comorbidity, medications, biomarkers, pain, nutrition, strength, balance, gate, physical environment, hearing, vision, cognitive ability, motivation, and behavior, along with contextual factors such as demographic and socioeconomic factors, especially in Brazil, may work synergistically to impact ADL/IADL, falls, hospitalizations, and death as people age. The IC measure and its domains capture the complexity of the 14 factors’ interactions, allowing for the evaluation of the effect of not only each factor but also their joint effect.

In addition, there is a pressing need in healthcare services for studies that assess the impact of effective health promotion strategies—cognitive stimulation, promotion of physical activity, and nutritional education—in preventing IC loss and maintaining FA in elderly people in Brazil. For this purpose, longitudinal observational studies are needed to initially assess these scientific assumptions and justify and guide future studies of controlled interventions.

This paper describes a proposal to 1) constitute a population cohort of elderly people living in a middle-class neighborhood in a large urban center in Brazil and 2) create a single indicator that expresses the trajectory of IC over the years. For this purpose, an assessment of the IC, the FA, and the social capital of the members at baseline and after 3 years will be carried out, establishing an average rate of IC decline, while controlling for the risk and protective factors—genetic, biological, clinical, behavioral, and environmental. The results will be vital for designing future interventional studies that prevent or mitigate functional ability losses associated with age. We intend, through the results from this cohort, to create an inclusive ecosystem of translational innovation in longevity integrated into a national/global innovation system in a continuous process of development and partnerships.

### Objectives

The cohort study proposed here addresses the determinants of IC and its relationships with FAs that allow longevity with good health and independence in everyday life. Considering that the literature on cohort studies that indicate IC values for the different aging trajectories is limited, we intend to build an IC index composed of the different domains, which can be validated as a risk indicator for classic outcomes such as hospitalization, falls, death, and severe dependence. We also intend to use the data to design clinical trials and nested case–control studies, with sample power, to evaluate measures aimed at preventing or mitigating functional ability losses over time.

To that end, we aim to1. Create a population cohort of people aged 60+ (LONGFUN) living in a middle-class neighborhood in a large urban center in Brazil.2. Create a composite IC index considering the five domains: cognitive, psychological, sensory, locomotor, and vitality.3. Carry out an epidemiological segmentation considering the index composed of IC and the sociodemographic, behavioral, and clinical factors.4. Identify the genetic and immunological biomarkers associated with each segment in a representative subsample of the cohort to be evaluated by a geriatric and multidisciplinary team that will define the needs of care for each segment.5. Analyze the trajectory of the IC composite index for the total cohort and for each segment created, seeking its predictive power as an indicator of risk for the main outcomes: hospitalization, disability, falls, and death.6. Monitor IC changes over time and the impact of the changes on baseline predictors.7. Propose strategies for the development of an integrated system for people-centered healthcare based on the identified needs for care.

## Methods

### Study design

The proposed study is a 3-year prospective cohort study of a population of older adults aged 60 years—the onset age designated by the World Health Organization (2015)—or older in the city of São Paulo, Brazil. The result will be a set of biological, social, clinical, and functional data that will allow the study of the progression of IC over time among this population and its associations with ADL, IADL, falls, hospitalization, and death.

### Study area and population

This cohort study is being proposed in the coverage population of the Basic Health Unit (UBS) Vila Mariana in the Southeast Health Coordination, an area adjacent to the area of influence of Hospital São Paulo in the Districts of Health and Vila Mariana in the city of São Paulo, where the previous cohorts of the EPIDOSO Project were selected (Ramos et al., 1998; Ramos et al., 2013). The study area has 156 census sectors (SC) and 39,104 households.

Based on the 2010 census of 100,000 inhabitants, approximately 15,000 seniors (aged 60+) residing in this area will be eligible for this study. The eligible and potential participants of the cohort represent an urban population with a good educational and socioeconomic level.

### Eligibility

All adults aged 60 and older living in the study area who will be contacted by the study team can participate in the study. Older adults residing in long-stay institutions for the elderly and those who are bedridden will be excluded from our study as the focus of this research is the follow-up of IC until the development of one or more outcomes: severe dependence, fall, hospitalization, or death as a function of IC. It will also be important to ensure through an initial in-house geriatric assessment that participants at baseline do not have significant loss of independence in the activities of daily living (ADL and IADL scores >0) (Katz and Akpom, 1976; Lawton and Brody, 1969) and cognitive ability (Clinical Dementia Rating (CDR) > zero) (Morris, 1994).

### Study sample size and power calculation

A census of the study area will randomly select 50 census sectors (CSs). All adults aged 60 years or older residing in these sectors will be invited to enroll in the cohort through a door-to-door visit (≈6,000 seniors ≥60 years initially listed). All those who will have been selected and would agree to participate and enroll will be evaluated with geriatric and gerontological assessment, including a battery of clinical exams. Based on the experience of previous cohorts, a refusal rate of ≈15% is expected from the older adults contacted, for an initial sample of approximately 5,500 participants (Figure 1).

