**FIGURE 1 F1:**
[figure not shown]
Proposed study design.

In a period of 6 months, we expect that a team of trained interviewers will contact all potential cohort participants. Based on information from a recent study on the association of IC with the outcome incidence rates of functional dependence, falls, and death (Prince et al., 2021), we developed sample size estimates for comparing two proportions that represent the rates of outcomes in the groups that are exposed (low IC) and unexposed (medium or high IC) (see Tables 1, 2). Calculations considered various effect sizes (relative risk) and incidence or mortality rates. In estimating the sample size needed for this cohort study, this study considered the incidence of the expected outcome in the unexposed cohort (high IC), the risk assumed in the exposed group relative to the risk of the unexposed group (RR), a specific level of confidence (1-α = 0.95; where α = type I error rate), and a specific value of the desired sample power (1-β = 0.80; where β = type II error rate) for the detection of significant differences between the two cohorts. The outcome incidence rate in the cohort was used as a proxy for the expected outcome incidence rate in the unexposed group (high IC). The summary tables (Tables 1, 2 below) provide sample sizes for extremes of the assumed incidence and mortality rate values and the respective relative risks based on the confidence intervals of these measures. A total sample size of approximately 5,500 individuals (assuming 2,750 per group) will be sufficiently robust to maintain the desired power under most diverse scenarios and varying parameters, even if the dropout rate reaches approximately equal to 15% in the two cohorts. The exception will be with very small estimates of the relative risk of death (RR ≤ 1.3).

**TABLE 1 T1:** Sample sizes for specific values of functional loss (FL), incidence, and relative risk for intrinsic capacity (IC) and FL.

	Average risk ratio	Low risk ratio	High risk ratio
Risk ratios (RR)	1.91	1.7	3.0
Incidence rate among the unexposed group	0.0495	0.04925	0.04925
Confidence level (1-α)	0.95	0.95	0.95
Power (1-β)	0.8	0.8	0.8
Study type	Cohort	Cohort	Cohort
Sample per group (n_i_)	514	816	138
Total sample (n_1_+n_2_)	1,028	1,632	276

**TABLE 2 T2:** Sample sizes for specific values of total mortality (TM) and relative risk for IC and TM.

	Average risk ratio	Low risk ratio	High risk ratio
Risk ratios (RR)	1.66	1.3	2.0

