#### Statistical models to assess whether IC is a predictor of ADLs/IADLs, falls, and death

Two Cox regression models will be evaluated to estimate the incidence rates of outcomes (i.e., functional loss measured by IADLs, falls, and death) associated with IC at baseline (e.g., TIC, DIC, and WIC) (ElHafeez et al., 2021). Cox’s first model has the indicator variable X to denote the association with each of the two groups of IC exposure at baseline (e.g., X1 = 1 for medium and high TIC and X1 = 0 for low TIC), with Y being the adverse incident at 3 years of follow-up (loss of ADLs/IADLs, falls, and death); survival times will be measured by the interval from the first assessment to the adverse incident. For subjects who do not experience an adverse incident, the follow-up time will be the last evaluation of the study.

The model also comprises a collection of covariates V with the potential to be a confounding factor in the association between Y and X (e.g., sociodemographic factors), and W would be the potentially interactive term between X and V (e.g., sex * TIC). The regression coefficient of X describes the effect of TIC on outcome Y, that is, the risk of greater or lesser loss of ADL/IADL, falls, and death for those exposed to medium or high TIC relative to those exposed to low TIC. The W terms will assess whether there is a positive interaction between TIC and one of the V confounders that have been identified to be potentially interacting. The model will extend by substituting TIC for DIC or WIC as the main exposure variable X. Alternatively, we can also model Y (e.g., IADL) as a function of X (either TIC, DIC, or WIC) and the same set of V and W using logistic regression to estimate the odds ratio of the outcomes.

We will evaluate the IC trajectory through changes in IC scores (∆IC or WIC) or the presence of IC decline (DIC) after 3 years, along with their associations with IADL outcomes, falls, and death. For example, the mean/median of ∆IC (or WIC) and the prevalence of DIC will be generated at baseline and at the end of the 3-year follow-up. We will then generate the mean/median or prevalence of IC measure by levels of ADL/IADL, falls, and death. The means/medians of IADLs and the incidence of falls and death after 3 years of follow-up will also be estimated.

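### The cohort samples 50 whole census sectors, but the sample size and the stated models ignore sector clustering; the cost falls mainly on means, prevalences, incidences and the ∆IC = 0 test

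*Protocol article*

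**What the plan says.** On the frame, the section on study area and population states: "The study area has 156 census sectors (SC) and 39,104 households". It puts the eligible population at "approximately 15,000 seniors (aged 60+) residing in this area will be eligible for this study".

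On sampling, the section on sample size and power makes the sector the random unit ("A census of the study area will randomly select 50 census sectors (CSs") and takes everyone eligible within it: "All adults aged 60 years or older residing in these sectors will be invited to enroll in the cohort through a door-to-door visit". The planned cohort is about 5,500.

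On sample size, the same section describes "sample size estimates for comparing two proportions that represent the rates of outcomes in the groups" with low versus medium or high IC. Tables 1 and 2 give the resulting numbers at 95% confidence and 80% power. The text concludes that 5,500 (2,750 per group) keeps the desired power in most scenarios even with about 15% dropout, except for death at RR ≤ 1.3. No ICC or design effect appears.

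On analysis, the section on IC as a predictor begins: "Two Cox regression models will be evaluated to estimate the incidence rates of outcomes". Its models contain the IC exposure, covariates V and interactions W. The logistic and ordinal models elsewhere in the data-analysis text are built the same way. No sector-level random effect, frailty, cluster-robust variance or survey design is mentioned.

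**The concern.** People in the same sector share surroundings, services and social position, so their outcomes tend to be correlated. When whole sectors are drawn, the number of sectors limits precision as well as the number of people. A variance formula that counts 5,500 independent participants then understates uncertainty.

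This touches the study's own first aims. The rationale wants an average rate of IC decline, research question 1 tests ∆IC = 0, and the analysis section promises means of ∆IC, prevalence of IC decline and incidence of falls and death. Each is a single-sample estimate, and such estimates carry the full design effect. At stake are confidence intervals that cover less often than stated and a test of decline that rejects too often.

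**Working it through.** **1. Reproduce the tables.** Two independent proportions, two-sided α = 0.05, power 0.80, equal groups, unpooled variance:

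n per group = (1.96 + 0.8416)² × [p₀(1 − p₀) + p₁(1 − p₁)] / (p₁ − p₀)², with p₁ = RR × p₀.

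| Scenario | p₀ | RR | Computed n | Printed n |
|---|---|---|---|---|
| Functional loss | 0.0495 | 1.91 | 514 | 514 |
| Functional loss | 0.04925 | 1.7 | 816 | 816 |
| Functional loss | 0.04925 | 3.0 | 140 | 138 |
| Death | 0.04826 | 1.66 | 926 | 926 |
| Death | 0.04826 | 1.3 | 3,922 | 3,922 |
| Death | 0.04826 | 2.0 | 449 | 432 |

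The two cells that differ (138 and 432) come out exactly with p₀ = 0.05, so they look like rounding of the rate. All six cells are explained by the independence formula, with no allowance for clustering.

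**2. Cluster size.** 5,500 / 50 = 110 per sector at enrolment. After 15% dropout, 4,675 remain: m = 4,675 / 50 = 93.5 per sector and 2,337.5 per group.

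**3. One-sample quantities.** Design effect DE = 1 + (m − 1) × ICC. The true size of a nominal 5% test is 2 × [1 − Φ(1.96 / √DE)]. The ICC values are assumptions, because the article gives none.

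| ICC | DE | SE ratio √DE | Effective total n (4,675 / DE) | True size of 5% test |
|---|---|---|---|---|
| 0.005 | 1.46 | 1.21 | 3,197 | 10.5% |
| 0.01 | 1.93 | 1.39 | 2,429 | 15.8% |
| 0.02 | 2.85 | 1.69 | 1,640 | 24.6% |

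**4. Finite-population correction.** Sampling 50 of 156 sectors (32%) leaves a factor of 1 − 50/156 = 0.679 on the sector component if inference stops at this area. DE = (1 − ICC) + m × ICC × 0.679 gives 1.31 at ICC 0.005 and 2.25 at ICC 0.02, so the test runs at about 9% to 19%.

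**5. IC group versus outcome.** IC varies between people within a sector, so the suitable approximation is DE = 1 + (m − 1) × ICC of exposure × ICC of outcome. For assumed exposure ICC 0.01 to 0.10 and outcome ICC 0.01 to 0.05:
- lowest: 1 + 92.5 × 0.01 × 0.01 = 1.01
- highest: 1 + 92.5 × 0.10 × 0.05 = 1.46, with standard errors 21% larger

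Across that range, power is at least 0.957 in every scenario except death at RR 1.3.

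**6. Power under the upper bound.** Applying the full design effect of step 3 to the group contrast, with 2,337.5 / DE effective per group:

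| ICC | Death RR 1.66 | Functional loss RR 1.7 | Functional loss RR 1.91 | Death RR 2.0 |
|---|---|---|---|---|
| 0 | 0.99 | 1.00 | 1.00 | 1.00 |
| 0.01 | 0.89 | 0.93 | 0.99 | 1.00 |
| 0.02 | 0.75 | 0.80 | 0.94 | 0.97 |

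Functional loss at RR 3.0 stays at or above 0.998 even at ICC 0.05. Death at RR 1.3 has power 0.58 under independence, in line with the article's own exception. Death at RR 1.66 needs 1,852 in total, so the design effect can reach 4,675 / 1,852 = 2.52 before power falls below 0.80. That corresponds to ICC = 1.52 / 92.5, about 0.016.

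**The case against.** The strongest reply is that no sample-size conclusion changes. Outside the excepted cell the tables need at most 1,852 people against 4,675 retained, and the full design effect is only an upper bound for an exposure that varies within sectors. This stands. A reader might infer that the power statement is broken, but the figures do not support that.

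A second reply is that this is a condensed article, and a variance estimator may sit in a fuller plan. This stands in part. The data-analysis section also allows robust methods if model assumptions fail, but it is generic and does not name clustering. The sample-size basis is nevertheless fixed here under independence, and the models are set out term by term without sector.

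A third reply is that the inflated test size rests on assumed ICCs. That is fair. ∆IC is a within-person change in which stable sector differences cancel, so its ICC may lie at or below the low end of the range. The finite-population correction helps further, but only for inference about this area, and the article frames its findings for older people in São Paulo and Brazil.

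Two further inferences should not be drawn:
- The text does not enrol whole households. It invites residents aged 60 or over, so seniors who share a home may both enter. With about 15,000 seniors in 39,104 households (0.38 per household), such clusters are small.
- The adjustment for socioecological context does not bring in sector-level covariates. The examples given, such as sociability and numbers of family and friends, describe persons.

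**Conclusion.** The concern holds for the variance of one-sample estimates. The design is a cluster sample, the sample size assumes independence, and no stated model recognises the sector. For an assumed ICC of 0.005 to 0.02 and 93.5 retained per sector, standard errors for mean ∆IC, prevalence of decline and incidence of falls and death should be 1.2 to 1.7 times the naive ones. The 5% test of ∆IC = 0 would run at about 10% to 25%, or 9% to 19% with the finite-population correction; for ∆IC itself the lower end, or less, is the more likely.

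For the IC-outcome contrast the effect is small to moderate, and the 80% power claim survives plausible clustering outside the exception already made. It would first fail at an ICC of about 0.016 (death, RR 1.66), and only if the full upper-bound design effect applied. This is a correction worth making before data collection, not a flaw that undermines the design.

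**What to change.** State that all models and all descriptive estimates use the sector as the cluster. In SAS, which the article names, this can be PROC PHREG with COVS(AGGREGATE) and sector as the ID, or the SURVEY procedures with a CLUSTER statement for means, proportions, logistic and Cox models. The ordinal model for ∆IC needs a sector-level sandwich variance or a bootstrap that resamples sectors. Fifty sectors are enough for a sandwich estimator. If a finite-population correction is used, say that inference is then limited to the study area.

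In the sample-size section, add a design effect over a stated ICC range, and say which form applies to the group contrast and which to the single-sample estimates.

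The cost is a few lines of code and text, somewhat wider intervals and a slightly less favourable power statement. Sector membership is known from the sampling, so no new data are needed and enrolment does not change. The article reports that no data have yet been collected, so the change can be made in advance.
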